## Treatment of Adverse Events

Treatment of any AE is at the sole discretion of the PI or the LMM and should be in accord with accepted, local standards of good medical practice. The applied measures should be recorded in the subject record. The recording of AEs is an important aspect of study documentation. The PI is responsible for ensuring documentation of all AEs according to the detailed guidelines set out herein. The subjects’ parents will be instructed to contact the PI or his designees immediately should a subject manifest any sign or symptom perceived as serious.

# SUBJECT COMPLETION and DROP-OUT

## Definition of a Drop-out

From the perspective of data analysis, a 'drop-out' is any subject who is not brought back for the concluding visit foreseen in the protocol. Any subject who has not completed all three immunizations will, if the parent/guardian is willing, still be followed for the entire study period. Any such subject who is brought in for the concluding visit foreseen in the protocol is considered to have completed the study and is therefore not considered a dropout.

## Procedures for Handling Drop-outs

Investigators will ensure that attempts will be made to contact parents of those subjects who have not been brought in for scheduled visits or follow-up. If, however, a parent has withdrawn parental consent, and if he or she requests no further home follow-up visits, the investigators will honor that request and no further procedures will be required of the subject. (In that case, the parents will be advised to seek treatment in future at the Kombewa Sub-District Hospital or other local health facility.) The reason(s) for withdrawal will be solicited from the parents. This information will be described on the Study Completion CRF.

## Reasons for Drop-outs

The Study Completion CRF will specify which of the following possible reasons were responsible for drop-out of the subject from the study:

- - Withdrawal of parental consent, due to a serious adverse event (SAE)
  - Withdrawal of parental consent, due to an adverse event (AE)
  - Withdrawal of parental consent, not due to an AE or SAE
  - Protocol violation (Specify)
  - Migration of family and/or subject from the study area
  - Loss to follow-up, cause unknown
  - Withdrawal by PI, due to a serious adverse event (SAE)
  - Withdrawal by PI, due to an adverse event
  - Other (Specify)

# DATA MANAGEMENT and ANALYSIS

Data entry will be performed on site at the WRP Kombewa Clinic. The CRCs will remove duplicate CRF pages periodically after review and/or approval of the study monitors and will submit to the data entry center. Statistics Collaborative, Inc., Washington, DC, USA will perform data analysis and reporting.

## Study Endpoints

### Primary Endpoint

The primary endpoint is time to first clinical episode of *P. falciparum* malaria meeting the “Primary Case Definition” given in Section 7.3. Time is measured from 14 days after administration of the third dose of study vaccine (SD 71).

### Secondary Endpoints

Because this is a Phase IIb trial, it has many secondary endpoints. Their purpose is to gain insight into the efficacy of the vaccine and to help define a primary endpoint for a confirmatory Phase III trial. They are not intended for use to make formal claims about the vaccine.

Measurements of efficacy during the EFP:

- Times to clinical episode of *P. falciparum* malaria meeting the various secondary case definitions shown in Exhibit 8
- Time to presence of asexual stage *P. falciparum* parasites during the six-month efficacy follow-up period
- Time to parasite density  50,000 asexual stage *P. falciparum* parasites per microliter of blood during the six-month efficacy follow-up period
- Number of clinical episodes of malaria, per subject, meeting the primary case definition
- Presence of MSP-1 3D7 parasites in clinical cases of malaria meeting the primary case definition
- Presence of MSP-1 3D7 parasites at a given cross-section survey time
- Time to anemia defined as Hgb < 8.0 g/dl, whether by active or passive case detection
- Proportion of subjects with anemia (Hgb < 8.0 g/dl)

Safety during the EFP:

- Occurrences of solicited AEs during a seven‑day follow-up period (vaccination day and six subsequent days) after each vaccination (five visits: vaccination day and days 1, 2, 3, and 6)
- Occurrences of unsolicited AEs during a 30-day follow-up period after each vaccination (vaccination day and 29 subsequent days)
- Occurrences of SAEs between the first vaccination and the end of the EFP

Immunogenicity during the EFP:

- Geometric means of MSP-1 Ab titers at Visits 2, 7, 12, 17, 20, and 23 (o/a Study Days 0, 29, 57, 85, 171, and 256)

### Tertiary Endpoints

This study has many tertiary endpoints. As with the secondary endpoints, their purpose is to gain further insight into the performance of the vaccine.

Measurement of safety (during the EFP and Addendum Efficacy Follow-up Period [AEFP]):

- Occurrences of SAEs between the first vaccination and the end of the study

Measurement of immunogenicity (during the EFP and AEFP):

- Geometric means of MSP-1 Ab titers at Study Days 0, 29, 57, 85, 171, 256, and 340

Measurement of efficacy and other biological effects by either active or passive detection (during the AEFP unless otherwise noted):

- Times to first clinical episode of *P. falciparum* malaria meeting the primary case definition (EFP and AEFP combined)
- Times to first malaria episode of *P. falciparum* malaria meeting the secondary case definitions in Exhibit 8 (EFP and AEFP combined)
- Time to presence of asexual stage *P. falciparum* parasites (EFP and AEFP combined)
- Time to parasite density  50,000 asexual stage *P. falciparum* parasites per microliter of blood (EFP and AEFP combined)

Number of clinical *P. falciparum* malaria episodes, per subject, meeting the primary case definition (EFP and AEFP combined)

- Presence of MSP-1 3D7 parasites in clinical cases of malaria meeting the primary case definition (EFP and AEFP combined)
- Presence of MSP-1 3D7 parasites at a given cross-section survey time (EFP and AEFP combined)
- Vaccine-induced GIA activity
- The parasite density at each episode of malaria infection meeting the primary and secondary definitions of clinical malaria and infection (see Exhibit 8)
- *P. falciparum* malaria allele types per malaria episode, meeting the primary and secondary definitions of clinical malaria and infection (see Exhibit 8)
- Times to first observation of anemia (Hgb < 8.0 g/dl), whether by active or passive case detection (EFP and AEFP combined)
- Hgb levels at all scheduled points of collection
- Proportion of subjects with anemia (Hgb < 8.0 g/dl) at each study collection
- Proportion of subjects with a documented decline in Hgb level of ≥ 20%
- Proportion of subjects with anemia (Hgb < 8.0 g/dl) at last study collection
- Number of cases of documented decline in Hgb level from baseline to last study sample collection
- Parasite density at all scheduled points of collection
- Non-3D7 parasite densities at all scheduled points of collection
- Genotyping for multiplicity of infections
- Antibody against fragments of MSP-142
- Antibody able to compete for binding to recombinant MSP-142
- Antibody able to inhibit secondary processing of MSP-142

## Study Cohorts and Data Sets to be Evaluated

### Total Cohort

For purposes of study data analysis, the “total cohort” will include all subjects enrolled in the study.

### Efficacy Cohort

For the purpose of study data analysis, two efficacy cohorts will be defined. The intention-to-treat (ITT) cohort will consist of all subjects who receive at least one dose of study vaccine or comparator vaccine. Given that children are to be randomized immediately before receiving their first dose of vaccine, the ITT and total cohort should differ by no more than a few children. For purposes of this ITT analysis, MBFs that are performed, read, and recorded between SD 0 and SD 71 inclusive (the first vaccination and 14 days after the third vaccination) will be archived and available despite falling outside the EFP and AEFP. The according-to-protocol (ATP) cohort will consist of subjects who receive all three doses of study vaccine or comparator vaccine, meet the inclusion/exclusion criteria, and do not have any important protocol violations.

### Safety Cohort

For purposes of study data analysis, the “safety cohort” will consist of all subjects who have received at least one dose of study vaccine or comparator vaccine and for whom any data on safety are available for analysis.

The presentations of safety data will explore separately the adverse experiences among subjects who received all three vaccinations and among those who received fewer; among those who received each of the three vaccine doses; and among those with clinically important violations of study protocol.

### Immunogenicity Cohort

For purposes of study data analysis, the “immunogenicity cohort” will include all subjects for whom assay results are available for antibodies against the specified study vaccine antigen component or the comparator. There are no standard cut‑off titers for seropositivity determinations in general use for the MSP-1 assay.

## Sample Size

Preliminary results from the WRAIR #1020 epidemiological study indicate that approximately 50% of children experienced at least one episode of clinical malaria in the first six months of follow-up. In this analysis, clinical malaria is defined as a parasite density  50,000 parasites per microliter in the presence of fever (axillary temperature  37.5 C). If one assumes that time to clinical malaria follows an exponential distribution, a 50% cumulative incidence rate corresponds to a hazard rate of 0.1155/month. A trial with 200 subjects per study arm, therefore, will have roughly 80% power to detect a 38% reduction in this hazard rate. A 38% reduction in the hazard rate corresponds to a 30% reduction in the six-month cumulative incidence rate. In terms of time to event, these rates imply that 25% of the subjects in the comparator group are expected to contract malaria within about 2.5 months from the third immunization; the comparable time for the FMP1/AS02A arm will be roughly 4 months. The median time to first clinical episode is expected to be 6 months and 10 months, respectively.

This sample size calculation is based on a two-sided 0.05-level logrank test. It assumes that children receive 3 doses of vaccine and then are followed for 6 months after the third dose. Cases of malaria are counted after the third dose of vaccine. Twenty percent of children are assumed to dropout during the immunization period. No further dropouts are assumed during the efficacy follow-up period.

## Final analyses

This section describes the analyses planned for the primary and secondary endpoints as well as for the most important of the tertiary endpoints. A Reporting and Analysis Plan (RAP) will be prepared before all subjects reach SD 240 and the study is partially unblinded. The RAP will describe the data analyses in fuller detail.

### Analysis of Demographics

Demographics characteristics such as age, gender, baseline bed net usage, and hemoglobin genotype will be tabulated by vaccine study arm. For continuous variables, means, standard deviations, and ranges will be calculated. For binary variables, frequencies and percentages will be computed.

### Analysis of Test Article Efficacy

The effect of FMP1/AS02A on clinical and biological endpoints will be analyzed as outlined below. For time-to-event analyses based on the six-month efficacy follow-up period, time is measured from 14 days after administration of the third dose of study vaccine (SD 71). Subjects will be censored at the time they become lost to follow-up or at the end of the efficacy follow-up period (SD 240), whichever occurs first. Loss to follow-up will also reflect death and moving away from the study area. Adjustments to time at risk will be made for anti-malarial usage and temporary absence from Kombewa. For time-to-event analyses based on the ten-month efficacy follow-up period, time will be measured from 14 days after administration of the third dose of vaccine. Subjects will be administratively censored at SD 364. For time-to-event-analyses based on the ITT cohort, time is measured from time of randomization (SD 0).

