**Days 115 to 364  14 WRP KC Visits**

***Visits 18-27***

- Monthly WRP KC visits will fall o/a Study days 115, 143, 171, 200, 228, 256, 284, 310, 340, and 364 (all ± 14)
- Beginning on study day 115, parents/subjects will visit the WRP KC monthly ± 14 days for interim history, including history of fever in 24 hours, axillary temperature, and 1 ml blood sample collection for MBF, CBC, and 3D7 allotyping
- On Study days 171, 256, and 340, an additional 1 ml of blood will be collected from which serum for anti-MSP-1 antibody titers will be aliquoted
- Check concomitant medications
- History-directed physical exam
- Parents/subjects will continue to attend the WRP KC whenever the latter are sick
- Any deaths, out-migrations, absences from Kombewa, and antimalarial usage will be documented

Exhibit 6. Intervals Between Study Visits

| **Interval** | **Size of Interval** |
| --- | --- |
| ***(Visit 1********Visit 2)***  ***(Visit 2********Visit 6)*** | ***Variable***  ***6 ± 9 days*** |
| ***(Visit 2********Visit 7)*** | ***28 ± 9 days*** |
| ***(Visit 7********Visit 11)*** | ***6 ± 9 days*** |
| ***(Visit 7********Visit 12)*** | ***28 ± 9 days*** |
| ***(Visit 12********Visit 16)*** | ***6 ± 9 days*** |
| ***(Visit 12********Visit 17)*** | ***29 ± 7 days*** |
| ***(Visit 18********Visit 27)*** | ***29 ± 7 days*** |

Exhibit 7. Schedulea of Routine Subject Evaluations

| Clinic Visit | 1 | 2 | 3-6 | 7 | 8-11 | 12 | 13-16 | 17 | 18, 19 | 20 | 21, 22 | 23 | 24, 25 | 26 | 27 | FW 1-13 |
| --- | --- | --- | --- | --- | --- | --- | --- | --- | --- | --- | --- | --- | --- | --- | --- | --- |
| **Study Day** | **Scr** | **0** | **1,2,3,6** | **29** | **30, 31, 32, 35** | **57** | **58, 59, 60, 63** | **85** | **115, 143** | **171** | **200,228** | **256** | **284, 310** | **340** | **364** | **14-354** |
| Written Informed Consent | x |  |  |  |  |  |  |  |  |  |  |  |  |  |  |  |
| Verification of Eligibility Criteria | x | x |  | x |  | x |  |  |  |  |  |  |  |  |  |  |
| Medical Historyk | x |  |  |  |  |  |  |  |  |  |  |  |  |  |  |  |
| Weight | x |  |  |  |  |  |  |  |  |  |  |  |  |  |  |  |
| Respirations | x | x |  | x |  | x |  |  |  |  |  |  |  |  |  |  |
| Assign SID | x |  |  |  |  |  |  |  |  |  |  |  |  |  |  |  |
| Check SID |  | x |  | x |  | x |  |  |  |  |  |  |  |  |  |  |
| Interim Medical History |  | x | x | x | x | x | x | x | x | x | x | x | x | x | x |  |
| Physical Examination | x |  |  |  |  |  |  |  |  |  |  |  |  |  |  |  |

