### Definition of Symptomatic Malaria for Clinical Purposes

In the event that a subject presents to the WRP KC with fever (≥ 37.5ºC), history of fever during the past 24 hours, or any complaints that the attending clinician suspects are due to malarial infection, an MBF will be taken and read immediately to confirm the diagnosis, and a CBC will be performed. All subjects with asexual parasitemia will then be treated with antimalarials as indicated in Section 7.3.3.

Subjects found to meet any of the above criteria through active case detection will be evaluated by MBF and treated the same day, if appropriate.

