#### Biological effects

***Secondary endpoints***

*Time to presence of asexual stage P. falciparum parasites during the six-month efficacy follow-up period* – Similar analyses as those described for the primary endpoint will be performed.

*Time to parasite density  50,000 asexual stage P falciparum parasites per microliter of blood during the six-month efficacy follow-up period* – Similar analyses as those described for the primary endpoint will be performed.

*Presence of MSP-1 3D7 parasites in clinical cases of malaria meeting the primary case definition during the six-month efficacy follow-up period* – Frequencies and percentages of cases with circulating MSP-1 3D7 parasites will be calculated by vaccine study group.

*Presence of MSP-1 3D7 parasites at a given cross-section survey time during the six-month efficacy follow-up period* – For a given survey time, the frequency and percentage of subjects with circulating MSP-1 3D7 will be calculated by vaccine study arm.

*Time to anemia defined as hemoglobin level < 8.0 g/dl during the six-month efficacy follow-up period* - Similar analyses as those performed for the primary endpoint will be conducted. In addition, a Cox model with vaccine study arm, baseline hemoglobin, and age as covariates will be applied to the data. The six-month cumulative incidence rate of anemia will be calculated for each vaccine study arm.

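### The antimalarial time-at-risk adjustment is written for efficacy time-to-event analyses in general, so it also reaches time to anemia, an endpoint it does not suit

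*Protocol*

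**What the plan says.** Section 12.4.2 of the protocol (Analysis of Test Article Efficacy) opens with its scope: "The effect of FMP1/AS02A on clinical and biological endpoints will be analyzed as outlined below". It then gives the time origin, the censoring rules and the sentence at issue: "Adjustments to time at risk will be made for anti-malarial usage and temporary absence from Kombewa". That sentence names no endpoint and makes no exception.

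Time to anemia is listed in the same section under Biological effects, as a secondary endpoint at six months and a tertiary endpoint at ten months. In both places the instruction is "Similar analyses as those performed for the primary endpoint will be conducted", followed by a Cox model with baseline hemoglobin and age and a cumulative incidence. Section 12.1.2 defines the endpoint as "Time to anemia defined as Hgb < 8.0 g/dl, whether by active or passive case detection".

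Exhibit 7 has a row for exposure time variables. Its footnote groups antimalarial drug use with death, out-migration and absence from Kombewa.

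On treatment, section 7.3.2 says of children with suspected malaria that "All subjects with asexual parasitemia will then be treated with antimalarials as indicated in Section 7.3.3". Treatment is therefore wider than the primary case definition.

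**The concern.** The adjustment has a clear purpose for malaria endpoints: for a time after treatment a child is unlikely to develop a new parasitemia, so that time is not really at risk. Anemia is different. A treated child can still fall, or remain, below 8.0 g/dl, and malaria-related anemia may show after the episode. The protocol's own background makes the link: in the two Gambian pediatric trials (Mal-015 and Mal-020), all six children with moderate anemia had malaria documented by the time the anemia was recorded.

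The excluded time is also created by an outcome of randomization. If the vaccine reduces treated malaria, the arms lose different amounts of follow-up, at moments related to the child's hemoglobin. The analysis would then no longer describe the first occurrence of anemia as section 12.1.2 defines it.

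**Working it through.** **The plan's own figures.** The protocol gives no figure for the anemia endpoint or for the adjustment. Its sample-size statement concerns the primary endpoint only. It reproduces (80.0 + 55.9 = 135.9 events from 160 children per arm after 20% dropout; power 79.6% at a hazard ratio of 0.62, against the stated 80%) and has no bearing here.

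**What the adjustment could mean.** The text does not say. There are three plausible readings:
- Post-treatment time is removed and the child re-enters later. Anemia seen only in the gap is not counted; anemia that persists is counted late.
- The child is censored at treatment. All later anemia is lost.
- Time is removed but events in it are kept. The denominator no longer matches the events.

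None of the three suits anemia. Pairing antimalarial use with absence, in section 12.4.2 and in Exhibit 7, makes removal the most natural reading.

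**Illustration (invented child, assumed window).** A child is treated on study day 105, with Hgb 7.4 on day 115 and 8.6 on day 143. Under section 12.1.2 this is a case on day 115. With a 14-day exclusion, day 115 (10 days after treatment) is outside time at risk and no event is counted. With a 7-day exclusion the event counts. If Hgb were still below 8.0 on day 143, the 14-day rule would count it 28 days late.

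**Share of time removed.** With treated episodes at rate r per month and w months excluded per treatment, the share is rw/(1 + rw). Section 4.1 gives monthly attack rates of 20 to 55%. Taking these as treated-episode rates is an assumption, as are windows of 14 and 28 days. With a 30.4-day month:

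| r | window | rw | share removed |
|---|---|---|---|
| 0.20 | 14 d | 0.20 × 14/30.4 = 0.092 | 0.092/1.092 = 8.4% |
| 0.20 | 28 d | 0.184 | 15.6% |
| 0.55 | 14 d | 0.253 | 20.2% |
| 0.55 | 28 d | 0.507 | 0.507/1.507 = 33.6% |

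If each attack rate is instead read as a 28-day risk and converted to a hazard, −ln(1 − p)/28 per day, the shares are 10 to 29% for 14 days and 18 to 44% for 28 days. A 7-day window on that basis gives 5 to 17%, and no window gives nothing.

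**How often the next scheduled blood count falls in the window.** Nominal counts in the six-month period are on days 85, 115, 143, 171, 200 and 228. From day 71 the gaps are 14, 30, 28, 28, 29 and 28 days, 157 in all. For treatment spread evenly, the share is the sum of min(gap, w) divided by 157:
- 7 days: 42/157 = 27%
- 14 days: 84/157 = 54%
- 21 days: 119/157 = 76%
- 28 days: 154/157 = 98%

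**From time lost to cases lost.** This step needs the depth and timing of the fall in hemoglobin after malaria, which the protocol does not give. Simulations under two sets of assumed kinetics put the loss at 25 to 43% and at 32 to 82% of control cases. The arm ratio moved by up to about 0.1 in either direction in one, and by up to about 0.3, mostly toward no effect, in the other. That spread shows how far the answer depends on the assumptions; neither figure is an estimate for this trial.

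**The case against.** The strongest reply is that the harm is inferred. The protocol states no window, does not say that time is removed, and has no rule to disregard events. Section 12.4 leaves fuller detail to a Reporting and Analysis Plan written before unblinding, which is not at hand. The primary-endpoint paragraph to which the anemia analysis refers lists the logrank test, Cox model, Kaplan-Meier curves and cumulative incidence without mentioning the adjustment, and similar need not mean identical.

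Much of this stands. The length and mechanics of the window can properly wait for that plan. The scope is another matter: the protocol already states it, for clinical and biological endpoints together, and states it too broadly for anemia.

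The reply is also right about how much is protected. When a child presents with suspected malaria, "an MBF will be taken and read immediately to confirm the diagnosis, and a CBC will be performed", so anemia already present at the episode is recorded then. Anemia that lasts can be found at a later monthly count. The proportion with anemia (section 12.1.2) and the hemoglobin-level endpoints (section 12.1.3) do not use time at risk. Section 12.1.2 adds that secondary endpoints are not meant to support formal claims.

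**Conclusion.** The point holds as a minor flaw in a secondary and a tertiary analysis. The antimalarial adjustment, as written, covers time to anemia, and it is unsuitable there whatever the window, because treatment follows malaria and does not end the risk of Hgb below 8.0. On the assumptions of 14 to 28 days per treatment and 20 to 55% treated episodes per month, about 8 to 34% of control time would be removed. The effect on the anemia comparison cannot be sized from the protocol.

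A reader might infer more: that anemia in the weeks after a treated episode is simply not counted, so that the analysis drops malaria-related anemia and keeps the rest. The documents do not support that. They contain neither a window of weeks nor a rule to discard events; anemia on the sick-visit count and persistent anemia can still be counted; and no consistent direction of bias has been shown. The primary endpoint, its test and its power are untouched.

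**What to change.** In section 12.4.2, limit the antimalarial time-at-risk adjustment to the malaria and parasite endpoints: clinical episodes, presence of asexual parasites, and density of at least 50,000 per microliter. For the six-month and ten-month time-to-anemia analyses, state that children stay at risk during and after antimalarial treatment, with adjustment only for absence and loss to follow-up. The Reporting and Analysis Plan can then define the window for the endpoints where the adjustment belongs.

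The cost is one or two sentences. No new data, visits or procedures are needed, and patient care does not change.
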